### Compliance and drop-outs

Compliance is monitored through follow-up telephone calls and will be reported. Adherence to the intervention is examined at the patient's 3 month visit and an additional session with the nutritionist is arranged if necessary to provide additional dietary advice, recalculation of energy requirements and for encouragement. This also provides an opportunity to address any problems or difficulties being encountered by the patient, and to provide feedback. The number of patients that drop-out and their reasons for doing so will be documented but following the intent to treat analysis they will be included in data analysis until the point of drop-out. Differences in dropout rates and the reason for drop out will be assessed by group (intervention versus control).

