### Sample size

This study is an exploratory one and so formal power calculations are difficult. The primary endpoint used to calculate sample size was body composition. Smith *et al *[17] presented data from a study of prostate cancer patients treated with hormone therapy and the mean percentage change in fat mass following ADT treatment was 9.4% (SD = 9.6%). If it is assumed that the controls in the planned study will have a similar percentage of fat mass, then with 36 patients in the intervention group and 36 patients in the control group the study will have 90% power at 5% significance to detect a mean percentage change in fat mass of 7.4% between the control and intervention group. An additional 30% was added to the sample size calculation to account for non-compliance and potential drop-out or discontinuation. Therefore 47 patients will be randomised to the intervention and 47 randomised to the control group. This sample size will also allow us to detect a 3.4 point (SD = 5.0 points) difference in Fatigue Severity Score [8] (a 3 point difference on the fatigue scale is considered to be the minimal clinically important difference) [18]; and a 6.0 point (SD = 9.0 points) difference on the Functional Assessment of Cancer Therapy-General (FACT-G) score [8].

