### Quality control

Following the initial visit, patients are contacted by phone every 2 weeks for the first 3 months and every 3 weeks thereafter to monitor progress and compliance with the intervention and to record any possible adverse events. The control group is also contacted every 6 weeks, for a general discussion about their condition. To standardise the follow-up call a written check-list has been used and relevant information (walking steps from the previous week and their goal for the current week, illness etc.) are collected. Each participant is encouraged to bring their partner or care-giver on the day of data collection and to be present for the nutritionist's visit at their home to help to answer questions regarding dietary intake and food preparation for those who may not be actively involved in food shopping and cooking. It is also hoped that by involving the patient's partner/care-giver, the patient is encouraged to comply with the intervention at home. The baseline and follow-up (3 month and 6 month) body composition measurements are completed by the same person to avoid inter-interviewer bias. However, this person is not masked to treatment assignment. Although it is preferable to have any subjective measurements, such as body composition measurements, taken by a person who is masked to treatment allocation, this was not possible in the present study and in order to minimise any bias that may be introduced, all body measurements are taken and recorded without referring to the previously recorded measurements.

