### Statistics

The data collected in the trial will be analysed based on intention to treat and lost to follow-up cases will be considered as missing observations [38]. Change over the treatment period will be calculated by subtracting the baseline value from the value at month 3 and month 6. Primary and secondary endpoints between those assigned to the intervention and control group will be compared using analysis of covariance (ANCOVA) with baseline scores included in the models as covariates. Skewed data will be log transformed prior to inclusion in the ANCOVA models. The trial outline conforms to the Consort statement guidelines.

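### The intention-to-treat label covers an available-case analysis at each visit, so the month-6 comparison ignores month-3 data and can be biased if drop-out is selective

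*Protocol article*

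**What the plan says.** The Statistics section says the data will be "analysed based on intention to treat and lost to follow-up cases will be considered as missing observations". It then fixes the response and the model: "Change over the treatment period will be calculated by subtracting the baseline value from the value at month 3 and month 6", with the arms "compared using analysis of covariance (ANCOVA) with baseline scores included in the models as covariates". Under Compliance and drop-outs, men who leave are to be handled so that "following the intent to treat analysis they will be included in data analysis until the point of drop-out". The same section adds a descriptive check: "Differences in dropout rates and the reason for drop out will be assessed by group (intervention versus control").

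The Sample size section makes room for losses: "An additional 30% was added to the sample size calculation to account for non-compliance and potential drop-out or discontinuation". Table 1 shows that every primary outcome is measured at baseline, 3 months and 6 months. The article names no imputation, repeated-measures model or sensitivity analysis.

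**The concern.** Intention to treat leads a reader to expect a comparison of all randomised men. Under the stated rules, a man who attends at 3 months and then leaves has no month-6 change and falls out of the month-6 ANCOVA. His 3-month result has been collected and says something about where he was heading, but it plays no part there.

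This matters if the men who leave differ in outcome from those who stay, and do so differently in the two arms or in different numbers. The arms do carry different burdens. Only the intervention arm is asked to change diet and to walk more, and it is telephoned every 2 and later every 3 weeks, against every 6 weeks for controls. If men gaining fat despite the programme left it more often, the month-6 difference would flatter the intervention. Comparing drop-out by arm would reveal unequal numbers but would not change the estimate.

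**Working it through.** **1. The plan's own figure.** Inputs from Sample size: difference 7.4, SD 9.6, 90% power, 5% significance (taken as two-sided). The two-sample formula gives 36 per arm, as stated (power 0.905 by the normal approximation, 0.897 by the t distribution). Inflation: 36 × 1.3 = 46.8, rounded to 47. So 11 of 47 men per arm (23%) can be lost before the number falls below 36. A true 30% loss leaves 47 × 0.7 ≈ 33 per arm and 87% to 88% power. Loss of power is therefore minor; the question is bias.

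**2. What the rules imply.** Change at month 6 is the month-6 value minus baseline. A man lost before month 6 has no such value, is treated as missing, and counts only up to drop-out. He is analysed at month 3 if he attended, and is absent at month 6. No sentence says this outright, but it follows from the two sections read together.

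**3. Bias formula.** Let p be an arm's drop-out share, and d the amount by which its drop-outs' mean fat change exceeds that of its completers. The completers' mean is the full-arm mean minus p × d. Measuring benefit as control minus intervention:

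bias = p_I × d_I − p_C × d_C

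This is zero when drop-out is unrelated to outcome, or when p and d are equal in both arms. It can take either sign.

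**4. Range with selection in the intervention arm only (d_C = 0).** The document gives neither p nor d for outcome-related drop-out, so these are assumptions, with d from 2 points up to one SD (9.6).

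| p_I | d_I = 2 | d_I = 9.6 |
|---|---|---|
| 10% | 0.2 | 1.0 |
| 23% (11/47) | 0.5 | 2.2 |
| 30% | 0.6 | 2.9 |

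Against 7.4 points, this runs from about 3% (0.2/7.4) to 39% (2.9/7.4).

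**5. Type I error.** Simulation with 47 per arm, no true effect, drop-out depending on the month-6 value, and a t-test standing in for ANCOVA:
- non-selective drop-out, or equal selection at equal rates: about 5%;
- intervention arm only, 0.5 to 1 log-odds per SD, 23% to 30% drop-out in that arm: 7% to 18%;
- same selection in both arms (1 log-odds per SD), drop-out 30% intervention and 10% control: about 11%.

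**6. Would month-3 data help?** Simulation with a true month-6 difference of 7.4. Assumed: SDs 7 and 9.6 at months 3 and 6, correlation 0.7, month-3 means 1.0 (intervention) and 4.7 (control), everyone seen at month 3, and later drop-out depending on the month-3 change.

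| Drop-out | Available-case | Likelihood with month 3 |
|---|---|---|
| Intervention only, slope 0.2 per point (about 25% lost); control 23% at random | 9.2 | 7.4 |
| As above, slope 0.1 | 8.3 | 7.4 |
| As above, slope 0.05 | 7.8 | 7.4 |
| Slope 0.2 in both arms, equal rates | 7.4 | 7.4 |
| Slope 0.2 in both arms, higher rate in control | 6.6 to 6.7 | 7.4 |

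The two estimates had similar precision (SD about 2.2). The last row shows bias against the intervention.

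**The case against.** The strongest reply is that nothing in the document shows drop-out will be selective or unequal, so the bias is hypothetical. That stands. A reader might infer that the month-6 result will be biased, and biased in favour of the intervention; the document supports neither. The promise to compare drop-out by arm is a reporting safeguard, not an admission that the arms will differ. The statement that "However, this person is not masked to treatment assignment" concerns whoever takes the body measurements and says nothing about who leaves.

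The 30% allowance covers non-compliance as well as drop-out, and a non-complier who attends at month 6 is still analysed, so it cannot be read as a drop-out rate. A reader might treat the whole allowance as lost men with no benefit at all. That is an extreme case without support in the text, and a repeated-measures model would not fully correct it.

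The simulations rest on assumed inputs. A slope of 0.2 with SD 7 is 1.4 log-odds per SD, which roughly quadruples the odds of leaving and is strong selection; the resulting 1.8-point bias is still below the estimate's own SD. The likelihood analysis recovers 7.4 because drop-out was made to depend only on month-3 values that everyone had.

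Finally, the trial is described as exploratory, and an article leaves much to a fuller plan. That excuses missing modelling detail. It does not dispose of the point, because the article states a rule and a label, and the two do not match. A fuller plan that used a mixed model or imputation would be changing the stated rule.

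**Conclusion.** The point holds in a limited form. The stated rules produce an available-case analysis at each visit under an intention-to-treat label, and collected month-3 data do not inform the month-6 comparison. Completer analysis would be the wrong name, since men who leave after month 3 are still used at month 3. Nor does the article name month 6 as the main time point, so the consequence concerns the end-of-intervention comparison rather than a declared primary one.

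The month-6 difference can be biased, in either direction, if drop-out depends on outcome differently by arm or occurs at different rates. The size rests wholly on assumption: 0.2 to 2.9 points on 7.4 if selection is confined to the intervention arm, and about zero if it is absent or equal. The case for changing the method is that the alternative stayed at about 7.4 in every scenario of step 6, with similar precision.

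**What to change.** For each primary outcome, replace the ANCOVAs at months 3 and 6 with one likelihood-based repeated-measures model. Include all randomised men with any follow-up value, with terms for treatment, visit, treatment × visit and baseline × visit, and report the month-6 contrast from it.

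Add one delta-adjusted sensitivity analysis, in which the missing values are shifted by a stated amount. It is needed because the model cannot recover men lost before month 3, or drop-out that depends on unobserved values.

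If the present analysis is kept, describe it as available-case at each visit rather than intention to treat.

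The cost is revised wording and a little more analysis work. No new visits or measurements are needed, since Table 1 already schedules the month-3 data.

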### Data storage and confidentiality

All questionnaires are stored in a locked cabinet in a locked room, and have a unique identification number. Consent forms are stored separately from study questionnaires in a locked cabinet. Only anonymised data is entered into the computerised study database, and access to the database is restricted to the study team. Data will be stored for 17 years according to rules of the Belfast Health and Social Care Trust.

### Statistics

The data collected in the trial will be analysed based on intention to treat and lost to follow-up cases will be considered as missing observations [38]. Change over the treatment period will be calculated by subtracting the baseline value from the value at month 3 and month 6. Primary and secondary endpoints between those assigned to the intervention and control group will be compared using analysis of covariance (ANCOVA) with baseline scores included in the models as covariates. Skewed data will be log transformed prior to inclusion in the ANCOVA models. The trial outline conforms to the Consort statement guidelines.

### Ethical considerations

The study protocol has been approved by the Office for Research Ethics Committees Northern Ireland (ORECNI), the Research Governance of Belfast Health and Social Care Trust and Queen's University Belfast. Permission to contact patients is received from the consultants of the Northern Ireland Cancer Centre before approaching the patients. Informed written consent is collected from each participant. A telephone number and contact address is provided to patients for any queries they may have during the study period.

## Discussion

As far as we are aware, this is the first RCT to assess whether a combined diet and physical activity intervention can attenuate the negative changes in body composition associated with use of ADT in prostate cancer patients and also to assess its impact on fatigue and quality of life. The intervention period in the present study is longer than previous studies (12-20 weeks of physical activity interventions [8-11]) and, in keeping with current views that initiation and maintenance of a diet and physical activity modification for cancer survivors should be tailored to the survivor's condition and personal preferences [16], it is individually tailored to the patient. Moreover, patients' readiness to change lifestyle behaviours using the transtheoretical model is considered during the delivery of the intervention. This model has been used successfully in previous diet and exercise intervention studies [12,13,39]. We expect that by using these approaches we will increase compliance and achieve the greatest possible change in behaviour and in the outcomes of interest. The intervention is also home rather than hospital based and is therefore more likely to be sustained in this older population group [13,14,40,41]. Moreover, the study sample size is sufficient to detect a clinically relevant change in body composition and the study includes a range of validated physiological and psychological assessments, which will maximise the internal validity of the study.

The majority of ADT treated prostate cancer patients are overweight and obese [42]. Though we are not promoting a weight reducing diet, and weight reduction is not the primary goal of the intervention, it is likely that an improvement in dietary intake and a higher level of physical activity will result in modest weight loss in the intervention group. It is known that overweight and obesity is associated with an increased risk of chronic diseases including cardiovascular disease, diabetes, some forms of cancer and recurrence of cancer. Therefore, maintenance of weight or gradual weight loss in the intervention group can be viewed as a favourable outcome [43]. Because our intervention incorporates both dietary modification and physical activity, we will not be able to separate out the effects specifically attributable to either of these components. Furthermore, with no allocation concealment the control group patients will be free to change their diet and increase their physical activity; even though such behaviour may weaken any observed associations in the intervention arm.

The external validity of the study will depend on the representative of the patient population from which we recruit and on the proportion of eligible patients who agree to participate in the study. For logistic reasons, recruitment is limited to one centre, which is the regional oncology centre (in Belfast) and patients treated within this centre may not be representative of all prostate cancer patients treated with ADT. Also, the characteristics of recruited patients may be influenced by the study design e.g. patients who agree to take part in the trial may be more likely to be older or retired or highly motivated, as involvement in the study demands three additional clinic visits for outcome measurement. Patients living outside of the Belfast area may be more likely to decline in order to avoid more frequent journeys to the clinic and the associated additional costs that may be incurred. However, we are making every effort to arrange our follow-up visits to coincide with the patients' 3-monthly follow-up visits with their consultants to minimise travel. A positive aspect of our approach to recruitment is that potential participants have to be initially approached by their consultant which may lead to a better uptake than other approaches to recruitment e.g. community advertisement [44].

Thus study will determine whether a healthy life style intervention in prostate cancer patients can attenuate the adverse body composition changes associated with ADT. If successful, this intervention may lead to substantial and important changes in the management of prostate cancer patients.
